### Statistical analysis

4.5

Data processing uses SPSS statistical software version 17.0 (IBM Corporation). Normally distributed variables are expressed as mean and standard deviation; non-normally distributed variables are expressed as median and quartile range. Normally distributed variables between groups using independent sample *t* test, rather than the normal difference variables using Mann–Whitney *U* test. In the comparison group, paired *t* test variables were normally distributed, non-normally distributed variables the Wilcoxon rank sum test. *P* < .05 was considered a statistically significant difference. Study figures were created using SigmaPlot (Systat Software Inc.).

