### Sample size calculation

2.5

The study used SBDG and CV as the main outcome indicators. In the preliminary experiment, the mean value of SBDG between the 2 groups was 0.39, and the standard deviations of treatment group and control group were 0.28 and 0.35 respectively. On the other hand, the mean value of CV between the 2 groups was 0.41, and the standard deviations of treatment group and control group were 0.31 and 0.67 respectively. Set *α* to 0.05 and *β* to 0.1. The sample sizes calculated using PASS 11 software were 14 and 25, respectively. In order to ensure statistically meaningful results, considering the 20% dropout rate, and according to the formula of n ^ = n/(1–f), the total number of studies was determined to be 60 cases, 30 cases per group.

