## Outcome measures

4

We will collect the characteristics of the 2 groups of participants at baseline and after the intervention, such as age, sex, physical examination, biochemical indicators, and other data (twice in total). The primary outcome indicators and secondary outcome indicators are measured and calculated at baseline, the first month, the second month, and the third month, respectively. (Four times in total.)

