### Primary outcome measures

4.1

We will use the SDBG and CV as the main outcome measures.

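### The between-group test makes no adjustment for the baseline SDBG and CV that the trial collects; the test is valid, but it gives up precision that matters for CV

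*Protocol article*

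**What the plan says.** Section 4.1 of the protocol article names two primary outcomes: "We will use the SDBG and CV as the main outcome measures". Section 4 gives their schedule: "The primary outcome indicators and secondary outcome indicators are measured and calculated at baseline, the first month, the second month, and the third month". Section 4.3 repeats it and says that both are derived from 7-point finger-prick profiles. A baseline value of each primary outcome is therefore planned for every participant.

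Section 4.5 gives the method for comparing arms: "Normally distributed variables between groups using independent sample" t test, with a Mann-Whitney U test for variables that are not normal. Paired tests are for comparisons within a group. No covariate is named, and the section does not say whether the variable compared is the end value or the change from baseline.

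Section 2.5 plans both primaries with "Set *α* to 0.05 and *β* to 0.1", that is, 90% power. It gives pilot figures and 30 per arm including 20% dropout, but no correlation between baseline and follow-up.

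**The concern.** With about 24 completers per arm, a participant's baseline variability is likely to be the most useful predictor of later variability, and it costs nothing extra to obtain. A two-sample test on end values ignores it. A two-sample test on changes uses it with a slope fixed at 1, which is rarely the best slope. Either way the standard error is generally larger than it needs to be.

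The second issue does not depend on any correlation. If a normality check decides between the t test and the Mann-Whitney test, the quantity being compared (a difference in means or an ordering of ranks) is unknown until the data are seen. The two primaries could end up being tested for different quantities.

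At stake is the chance of detecting an effect on CV, where power is already below plan.

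**Working it through.** **Inputs (section 2.5).** For SDBG the text gives "the mean value of SBDG between the 2 groups was 0.39"; its pilot SDs are 0.28 (treatment) and 0.35 (control). For CV it gives "the mean value of CV between the 2 groups was 0.41"; its pilot SDs are 0.31 (treatment) and 0.67 (control). I read 0.39 and 0.41 as between-group differences, alpha as two-sided, and the stated sample sizes as per group. After 20% dropout, 30 × 0.8 = 24 per arm remain.

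**The plan's own figures.** n per group = (1.960 + 1.282)² × (s₁² + s₂²) / d².
- SDBG: 10.507 × (0.0784 + 0.1225) / 0.1521 = 13.9, so 14. This agrees with the stated 14.
- CV: 10.507 × (0.0961 + 0.4489) / 0.1681 = 34.1, so 35. The stated figure is 25.
- Dropout: 25 / (1 − 0.2) = 31.25, so 32. The stated figure is 30, which equals 25 × 1.2.

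**Unadjusted power at 24 per arm (noncentral t, 46 df).**
- CV: SE = √(0.545 / 24) = 0.1507; 0.41 / 0.1507 = 2.72; power 75.9%. The large-sample formula gives 77.7% and the Welch test 75.2%.
- SDBG: about 99%.

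The CV gap to the planned 90% is 90 − 75.9 = 14.1 points.

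**Adjusted CV power if the pilot SDs are end-value SDs (45 df).** The correlation r is my assumption, so a range is shown. Two versions bracket the result:
- Upper: variance falls by r² in each arm, so the sum of variances is 0.545 × (1 − r²).
- Lower: one pooled slope, the same r in both arms and a common baseline SD. The best slope then differs between arms in the ratio 0.67 / 0.31 = 2.2, so one slope fits neither arm exactly. The sum of variances becomes 0.545 − r² × (0.31 + 0.67)² / 2 = 0.545 − 0.4802 r², a fall of 0.88 r² (0.4802 / 0.545 = 0.88).

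| r | lower | upper | share of the 14.1-point gap recovered |
|---|---|---|---|
| 0.3 | 79.2% | 79.7% | 24–27% |
| 0.4 | 81.9% | 82.8% | 43–49% |
| 0.5 | 85.4% | 86.7% | 67–77% |
| 0.6 | 89.6% | 91.4% | nearly all or all |

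At r = 0.5 the gain equals having 28% (1 / (1 − 0.88 × 0.25)) to 33% (1 / (1 − 0.25)) more patients. On the upper version, 90% needs r of about 0.57.

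**Adjusted CV power if the pilot SDs are change-score SDs.** The 75.9% then belongs to a t test on changes. With equal variances at baseline and follow-up, ANCOVA multiplies the change variance by (1 + r) / 2:

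| r | power |
|---|---|
| 0.5 | 86.7% |
| 0.7 | 82.3% |
| 0.8 | 80.1% |

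Here the gain shrinks as r rises, but power stays above 75.9%.

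**Why the direction does not depend on the ambiguity.** Comparing end values fixes the baseline slope at 0, and comparing changes fixes it at 1. ANCOVA estimates the slope. The variance factors, 1 − r² against end values and (1 + r) / 2 against changes, are both at most 1.

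**The case against.** The case against has several parts, and much of it stands.

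- **The stated test is valid.** Under randomisation the unadjusted comparison is unbiased, and its standard error already allows for chance baseline imbalance. This stands: the point is about efficiency and a fixed target, not about error.
- **A reader might infer that adjustment would largely make up the CV shortfall.** The document does not support that. It gives no r, and at r = 0.3 only about 4 of 14 points are recovered. A high r should not be presumed, because each SDBG or CV value comes from 7-point finger-prick profiles and an SD from so few readings is noisy.
- **A reader might infer that baseline is wholly ignored.** Section 4.5 does not exclude a t test on changes, which would use baseline in part. Section 2.5 does not say which kind of SD the pilot SDs are. This stands, and it is why both cases are worked above.
- **The shortfall comes from section 2.5.** Its inputs give 35 per group where it states 25, and its dropout formula gives 32 where it states 30. Adjustment may offset this but does not correct it.
- **Covariates are often left to an analysis plan, which is not shown.** This carries less weight, because section 4.5 does not stay silent: it states which between-group tests will be used.

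**Conclusion.** The point holds as a recommended improvement. Section 4.5 states a valid but less efficient test although the baseline values are collected, and it lets the data choose between two targets. The size of the gain is conditional. With 24 per arm, CV power moves from about 76% to 79–80% (r = 0.3), 85–87% (r = 0.5) or 90–91% (r = 0.6) if the pilot SDs are end-value SDs, and to about 87% (r = 0.5) or 82% (r = 0.7) if they are change-score SDs. Under the end-value reading, most of the shortfall is recovered only if r is about 0.5 or more.

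These figures rest on an assumed r, the pilot differences and SDs as read above, a two-sided 5% test and 20% dropout. The claim that ANCOVA is never worse is a large-sample one under the usual common-slope model. For SDBG, power is no argument; the gain there is a tighter interval and a fixed target.

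**What to change.** In section 4.5, pre-specify as the primary analysis an ANCOVA of month 3 SDBG, and a separate one of month 3 CV, each on treatment and the baseline value of the same measure. Use heteroscedasticity-robust standard errors, because the pilot CV SDs differ between arms (0.31 and 0.67). Report the adjusted mean difference with its 95% confidence interval whatever a normality check shows. Keep the t or Mann-Whitney test as a sensitivity analysis.

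The cost is one degree of freedom and a change of wording, with no new data, visits or patients. The sample-size figures in section 2.5 need their own correction and should not be treated as settled by this change.

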### Efficacy evaluation

4.3

By calculating the SDBG and CV of the participants at baseline, the first month, the second month, and the third month, the efficacy will be evaluated (Table 2). At the same time, we will also evaluate MBG, LAGE, and PPGE, glycated hemoglobin as secondary efficacy evaluations. We will use a simple method is to get blood sugar and calculate the above indicators which is finger-prick measurements within a specific period, 7-point profiles (7 am, 9 am, 11 am, 1 pm, 5 pm, 7 pm, and 9 pm). Despite the lack of nocturnal blood glucose measurements, the SDBG can be an appropriate data even in data sets in which glucose values do not follow a Gaussian distribution, because it has a near linear relation with the interquartile range.^[27,28]^ In addition, we will measure the following indicators at baseline and at the end of the experiment: blood pressure, fasting plasma glucose, total cholesterol, low density lipoprotein cholesterol, high density lipoprotein cholesterol, triglycerides, advanced glycation end products, and changes in the scores of TCM syndromes measured by questionnaires.

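### SDBG and CV are measured at three post-baseline visits, but section 4.5 names only one-value-per-participant tests; a repeated-measures model would use the data more efficiently

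*Protocol article*

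**What the plan says.** Section 4.1 names two primary outcomes: "We will use the SDBG and CV as the main outcome measures". Section 4 says that primary and secondary outcomes are "measured and calculated at baseline, the first month, the second month, and the third month, respectively", which gives three post-baseline values per participant. Section 4.3 bases the judgement of efficacy on all of these visits: "By calculating the SDBG and CV of the participants at baseline, the first month, the second month, and the third month".

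Section 4.5 lists the tests:
- Between groups, the t test for normal data ("Normally distributed variables between groups using independent sample" t test) and, for non-normal data, the Mann-Whitney test ("rather than the normal difference variables using Mann–Whitney").
- Within a group, paired tests ("In the comparison group, paired" t test, or Wilcoxon).

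No primary visit, summary across visits or repeated-measures model is named. Section 4.4 requires evaluation indicators to be recorded when a participant withdraws, but no section says how a leaver's data enter the group comparison.

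**The concern.** The design collects three repeats of each primary outcome, while each named between-group test accepts one number per participant. If that number is the value at one visit, two things follow. The correlated information in the other two visits does not sharpen the comparison. And a participant with a month 1 or month 2 profile but no month 3 profile drops out of the month 3 comparison.

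What is at stake is precision, mainly for CV, the primary outcome with the larger stated sample size (25 against 14). A method fitted to the repeated-measures design would use data the trial already plans to collect.

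**Working it through.** **Inputs from section 2.5.** SDBG: difference 0.39, SDs 0.28 and 0.35. CV: difference 0.41, SDs 0.31 and 0.67. In each case the mean value quoted there is read as the between-group difference. "Set *α* to 0.05 and *β* to 0.1", so planned power is 90%; two-sided testing is assumed. Enrolment is 30 per group with 20% dropout, so 30 × 0.8 = 24 completers per group. The between-visit correlation r is not in the document and is assumed throughout.

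**1. The plan's own sample sizes.** n per group = (s1² + s2²)(1.960 + 1.282)² / d².
- SDBG: 0.2009 × 10.507 / 0.1521 = 13.9, so 14. This matches.
- CV: 0.5450 × 10.507 / 0.1681 = 34.1, so 35. The stated 25 does not follow. This is a separate point, but it sets the starting power below.

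**2. One visit, 24 per arm, Welch t test.**
- CV: SE = √(0.5450/24) = 0.151; 0.41/0.151 = 2.72 on about 32 degrees of freedom; power 75%. With 30 per arm it is 84%, and 36 per arm are needed for 90%.
- SDBG: SE = √(0.2009/24) = 0.0915; 0.39/0.0915 = 4.26; power about 99%.

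**3. Month 3 difference, using leavers' earlier visits.** Assume equal correlation between visits and, per arm, 24 completers plus 4 leavers seen at months 1 and 2 only. Months 1 and 2 explain R² = 2r²/(1 + r) of the month 3 variance. The variance relative to completers alone is (1 − R²) + R² × 24/28.

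| r | R² | Variance ratio | CV power |
|---|---|---|---|
| 0.4 | 0.229 | 0.967 | 77% |
| 0.7 | 0.576 | 0.918 | 79% |

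The variance falls by about 3–8%, and power rises from 75% to about 77–79%. No gain from baseline adjustment is counted, because section 2.5 does not say whether its SDs are of values or of changes.

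**4. Average of months 1–3, equal effect at each month, CV.** The variance factor is (1 + 2r)/3.

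| r | Factor | Power, 24 per arm | Power, 30 per arm |
|---|---|---|---|
| 0.3 | 0.533 | 95% | 98% |
| 0.5 | 0.667 | 90% | 95% |
| 0.7 | 0.800 | 84% | 91% |
| 0.9 | 0.933 | 78% | 87% |

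The average has a larger signal-to-noise ratio than month 3 alone only if the mean effect over the three months exceeds √((1 + 2r)/3) of the month 3 effect. That is 73%, 82% or 89% for r = 0.3, 0.5 or 0.7.

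**The case against.** A reader might infer more than the document supports.

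- **That each month is tested in isolation and the months are never combined.** Section 4.5 does not say so. A t test can be run on a participant's three-month mean, and the gain in step 4 comes from exactly such a test. Separate comparisons are the natural reading of the named tests, not a stated rule.
- **That leavers' earlier data are lost.** If visits are compared separately, a participant who leaves after month 2 is still in the month 1 and month 2 comparisons and is missing only from month 3. Nothing says the data are discarded, and section 4.4 has indicators recorded at withdrawal.
- **That this explains the low power for CV.** Most of the gap to 90% comes from section 2.5, whose own inputs need 35–36 per group.

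It can also be said that a two-sample test at one visit named in advance is valid, that an article may leave the visit contrast to an analysis plan, and that averaging changes the question from the end-of-course effect of a three-month treatment to a mean effect. The first and third of these stand. They limit the point to efficiency and argue against making the average the default. The second does not dispose of it, because section 4.5 does state its methods, and those methods fit poorly with the repeated visits fixed in sections 4 and 4.3.

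**Conclusion.** The point holds as one of inefficiency, not invalidity, and is worth acting on because the remedy is cheap. For CV with 24 completers per arm, the gain at month 3 is modest: about 2 to 4 power points, for assumed correlation 0.4–0.7 and 4 partial leavers per arm. The gain for the three-month average ranges from large (95% against 75% at correlation 0.3) to small (78% against 75% at 0.9), and it also needs a similar effect at every month. SDBG, at about 99% power from one visit, gains almost nothing. All these figures rest on a correlation the document does not give, on two-sided 5% testing, and on reading the quoted means in section 2.5 as group differences. A repeated-measures model does not replace correcting the CV sample size.

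**What to change.** In section 4.5, analyse SDBG and CV each with one linear mixed model for repeated measures:
- Use all available profiles at months 1, 2 and 3.
- Include group, month, group by month and the baseline value.
- Use an unstructured covariance, allowed to differ by group because the CV SDs are 0.31 and 0.67.
- Take the month 3 group difference from this model as the efficacy contrast.
- Add a transformation or a rank-based sensitivity analysis if residuals are clearly non-normal, so that the purpose of the present Mann-Whitney route is kept.
- Report the effect averaged over months 1–3 as a supporting contrast. If the sponsor wants the average rather than the end-of-course effect, name it as primary in advance.

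The cost is analysis wording and somewhat more modelling work, with no new visits or data. The sponsor should check that the software version named in section 4.5 can fit group-specific covariance. The averaged contrast is diluted if the effect builds slowly; the month 3 contrast is not.

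### Section 4.5 lets the observed distribution choose between a test of means and a test of ranks for SDBG and CV, although section 2.5 sizes the trial on means alone

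*Protocol article*

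**What the plan says.** The protocol article, section 4.5, gives the between-group rule in one sentence. It first assigns the independent-sample t test and then turns to the remaining variables: "rather than the normal difference variables using Mann–Whitney". The wording is rough, but the sense is clear: variables judged normal get the t test and the rest get Mann-Whitney. The descriptive summary follows the same switch: "non-normally distributed variables are expressed as median and quartile range". The rule covers all variables and makes no exception for the primary ones.

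Section 4.1 names two primary outcomes: "We will use the SDBG and CV as the main outcome measures". Section 4 has them "measured and calculated at baseline, the first month, the second month, and the third month, respectively". Two outcomes at three post-baseline visits make six between-group comparisons. That count is derived; the document does not state it.

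Section 2.5 plans on means and SDs only. For SDBG (spelled SBDG there), "the mean value of SBDG between the 2 groups was 0.39", with SDs of 0.28 (treatment) and 0.35 (control). For CV the corresponding figures are 0.41, with SDs of 0.31 (treatment) and 0.67 (control). The result is given as: "The sample sizes calculated using PASS 11 software were 14 and 25, respectively".

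**The concern.** A t test asks whether two means differ. Mann-Whitney asks whether values in one arm tend to rank above those in the other. When the data choose between them, neither the primary hypothesis nor its effect measure is settled until the data have been seen. If the choice falls on ranks, the report shows medians and a rank P value, and neither estimates the 0.39 or 0.41 on which the trial was sized. SDBG could be reported as a mean difference and CV as a rank comparison. If the check is made visit by visit, one outcome could also change its test between months.

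The two tests agree closely when the arms differ only by a shift. They part when the arms have unequal spread and skewed shapes. Section 2.5 itself reports unequal spread for CV.

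This is not a detail left to an analysis plan. The rule is written down, and the question is whether it is a good one.

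**Working it through.** **Inputs.** Section 2.5: differences 0.39 (SDBG) and 0.41 (CV); SDs 0.28 and 0.35, and 0.31 and 0.67; α 0.05 (taken as two-sided); β 0.1; 30 per arm with 20% dropout. Completers are 30 × (1 − 0.2) = 24 per arm.

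**1. Is the sizing mean-based?** The usual formula is n per arm = (1.960 + 1.282)² × (s₁² + s₂²) / d².
- SDBG: 10.51 × (0.0784 + 0.1225) / 0.1521 = 13.9, so 14. This reproduces the stated figure and confirms that 0.39 serves as a difference in means.
- CV: 10.51 × (0.0961 + 0.4489) / 0.1681 = 34.1, so 35. The stated 25 is not reproduced. That is a separate matter and nothing below rests on it.

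**2. How unequal are the spreads?** SDBG: 0.35 / 0.28 = 1.25. CV: 0.67 / 0.31 = 2.16.

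**3. What does the switch do to error rate and power?** The simulation used 3,000 trials per setting. The normality check was Shapiro-Wilk at 5% in either arm, which is an assumption because section 4.5 names no criterion. Data were normal, or gamma with skewness 1, with the control arm higher in the power runs. Entries are the share of trials with P < 0.05.

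| Setting | n per arm | t test | Mann-Whitney | Two-step rule |
|---|---|---|---|---|
| Equal means, equal SDs, normal | 24 | 0.052 | 0.051 | 0.057 |
| Equal means, equal SDs, skewed | 24 | 0.046 | 0.043 | 0.049 |
| Equal means, CV SDs, normal | 24 | 0.054 | 0.061 | 0.056 |
| Equal means, CV SDs, skewed | 24 | 0.059 | 0.104 | 0.101 |
| Equal means, CV SDs, skewed | 30 | 0.051 | 0.106 | 0.103 |
| CV difference 0.41, normal | 24 | 0.754 | 0.720 | 0.750 |
| CV difference 0.41, skewed | 24 | 0.780 | 0.634 | 0.693 |
| CV difference 0.41, skewed | 30 | 0.879 | 0.754 | 0.786 |
| SDBG difference 0.39, normal | 24 | 0.985 | 0.979 | 0.985 |
| SDBG difference 0.39, skewed | 24 | 0.991 | 0.992 | 0.992 |

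The Monte Carlo standard error is √(0.05 × 0.95 / 3000) = 0.004 near 5%, so the rise to 0.10 is not noise. Raising the skewness to 1.5 with the CV SDs and equal means gives about 14-17% for the two-step rule. A Welch test stays at 5-6%, like the t test. Repeat runs put two-step power for CV at 24 per arm at 0.68-0.71, against 0.79.

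The mechanism is simple. With right-skewed data and equal means, the arm with the wider spread has the lower median. The rank test picks up that gap although the means are equal. When control is both higher and wider, the same gap works against the planned difference, and power falls.

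**4. How often would the six comparisons mix tests?** Simulated share of trials, at 24 or 30 per arm and within-person correlation 0 to 0.8:

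| Assumed distribution | Check in each arm | Check on pooled residuals |
|---|---|---|
| Normal | 42-46% | 22-27% |
| SD of seven normal readings | 52-65% | 37-55% |
| Lognormal, relative SD 0.2-0.3 | 70-97% | 65-97% |
| Lognormal, relative SD 0.4 | 58-90% | 47-87% |
| Lognormal, relative SD 0.7 | 8-25% | 4-19% |
| Lognormal, relative SD 1.0 | 4% or less | 4% or less |

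At strong skew, mixing is rare because nearly everything goes to ranks, which the sizing did not assume.

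**The case against.** Four points can be made for the plan.

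- **Mixing is not established.** A reader might infer that the six comparisons will usually mix tests. The document does not support that: it gives no distribution for SDBG or CV, and the simulated share runs from 4% or less to 97%. The figures in section 2.5 could even point the other way. If both arms were lognormal with equal relative spread r, then (0.67 − 0.31) / r = 0.41 gives r = 0.88. At that spread CV would change test between months in only about 1-8% of trials. Section 4.5 also speaks of variables, so one classification per outcome is an open reading; SDBG and CV could then differ, but neither would change between visits. This objection stands, and the point is therefore put as may.
- **The error rate is not generally broken.** A reader might infer that any two-step rule misses its 5%. With identical distributions in both arms, it rejects in about 5-6% of trials. This stands too. The excess needs unequal spread together with skewness.
- **A rank test that rejects at equal means is not wrong on its own terms**, since the distributions do differ. True, but it then answers a question other than the one the trial was sized for.
- **The convention is common, and ranks can do better under skewness.** Also true: when the spread is similar in both arms, a mean comparison may lose a little power. That is a reason to keep the rank test as a supporting analysis, not to let the data select it.

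**Conclusion.** The point holds in this form: for SDBG and CV, the choice between means and ranks depends on the observed data, while the sample size rests on means alone. Test and effect measure may differ between primary comparisons, with a frequency that the document cannot settle.

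The measurable harm is conditional. For CV, with SDs of 0.31 and 0.67, equal means and skewness of 1 to 1.5, rejection is about 10-17% instead of 5-6%. Power at the planned difference is about 8 to 11 points lower at 24 per arm (0.79 − 0.71 and 0.79 − 0.68). With normal data both effects vanish. For SDBG, whose spreads are closer, the error-rate effect is small and power is about 0.98 or more with either test.

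These figures assume gamma-shaped data, Shapiro-Wilk at 5% in either arm and a two-sided 5% level. The skewness is an assumption; the SDs and differences are the protocol's. The change is worth making because it costs almost nothing, but the defect does not invalidate the design.

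**What to change.** In section 4.5, name one between-group method for SDBG and CV at every visit, before the first patient is enrolled: a comparison of means on the original scale allowing unequal variances (Welch), reported as a mean difference with a 95% confidence interval. This matches the quantities in section 2.5 and copes with the unequal CV spreads. Delete the normality check as the selector of the primary test. Medians and quartiles may still be shown as description.

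Keep Mann-Whitney, or an analysis of log values, as a sensitivity analysis only. A log-scale primary analysis would be a poorer match, because a ratio of geometric means does not estimate 0.39 or 0.41 either.

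The cost is a sentence or two of text and no new data. The downside is a small possible loss of power if the data prove heavily skewed with similar spread in both arms.

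### The rank test named alongside the paired t test is an independent-samples test; followed as written, it makes within-group P values for non-normal variables too large

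*Protocol article*

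**What the plan says.** Statistical analysis (4.5) lists two pairs of tests.

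- **Between groups.** Normal variables go to the independent-sample t test ("Normally distributed variables between groups using independent sample"). Non-normal variables go to the Mann–Whitney U test ("rather than the normal difference variables using Mann–Whitney").
- **A second comparison.** The opening words of this sentence are unclear, but it names the paired t test for normal variables and, for the others, "non-normally distributed variables the Wilcoxon rank sum test".

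Outcome measures (4) says that the primary and secondary outcomes are "measured and calculated at baseline, the first month, the second month, and the third month". Each participant therefore contributes a series of values, and any comparison over time within a group is paired. Efficacy evaluation (4.3) adds further indicators measured at baseline and at the end.

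The signed-rank test is not named anywhere in the article.

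**The concern.** The Wilcoxon rank sum test and the Mann–Whitney U test are the same test under two names, and both assume two independent samples. The section therefore names one independent-samples test twice, the second time as the counterpart of the paired t test. The rank test for paired data is the Wilcoxon signed-rank test.

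If the printed name is followed, the analysis ignores the pairing. When a participant's values correlate positively over time, the rank sum test assumes more variability in the difference than there is. Its P values are then too large, and real within-group changes are missed more often than they need be. A skewed variable would lose this power while a normal one, sent to the paired t test, would not. Non-normal data are a realistic prospect here: the Efficacy evaluation section itself discusses glucose values that are not Gaussian.

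**Working it through.** The plan gives no figure to reproduce on this point. The check has three steps.

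**1. Inputs**

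| Input | Value | Source |
|---|---|---|
| Participants per group | 30 | Sample size calculation (2.5): "the total number of studies was determined to be 60 cases, 30 cases per group" |
| Dropout | 20% | same section |
| Pairs left per group | 30 × (1 − 0.20) = 24 | arithmetic |
| Significance level | 0.05; two-sided is assumed because sidedness is not stated | Statistical analysis (4.5) |
| Before-after correlation r (log scale) | 0.3, 0.5, 0.7 | assumption; not in the article |
| True change for power | 0.5 SD on the log scale | assumption; not in the article |
| Distribution | log-normal, because normal variables would go to the paired t test | assumption |

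**2. Approximate type I error of the rank sum test on paired data**

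Under no change, positive correlation shrinks the true variance of the rank sum statistic by the factor 1 − ρ_S. Here ρ_S is the Spearman correlation, and for log-normal pairs ρ_S = (6/π) × arcsin(r/2). The test still uses the independent-samples variance, so in large samples

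actual type I error ≈ 2 × Φ(−1.96 / √(1 − ρ_S)).

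- r = 0.3: ρ_S = 0.288, error ≈ 2.0%
- r = 0.5: ρ_S = 0.483, error ≈ 0.6%
- r = 0.7: ρ_S = 0.683, error ≈ 0.05%

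**3. Simulation**

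The table uses 10,000 simulated data sets per setting, log-normal pairs with a log-scale SD of 0.6, and large-sample P values.

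| Pairs | r | Type I error, rank sum | Type I error, signed-rank | Power, rank sum | Power, signed-rank |
|---|---|---|---|---|---|
| 24 | 0.3 | 1.9% | 4.8% | 35% | 46% |
| 24 | 0.5 | 0.8% | 4.8% | 34% | 59% |
| 24 | 0.7 | 0.1% | 4.8% | 31% | 81% |
| 30 | 0.3 | 1.9% | 4.8% | 44% | 54% |
| 30 | 0.5 | 0.6% | 5.0% | 43% | 69% |
| 30 | 0.7 | 0.1% | 5.1% | 43% | 88% |

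The simulated rank sum error agrees with the formula. At r = 0 with 24 pairs it is 4.9%, so the distortion comes entirely from the correlation.

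Signed-rank power depends somewhat on skewness, because the test ranks raw differences. I repeated the 24-pair runs with 20,000 data sets at other log-scale SDs. Signed-rank power at r = 0.3, 0.5 and 0.7 was 48%, 61% and 82% at a log-scale SD of 0.4, and 44%, 57% and 76% at 1.0. A further run at 24 pairs gave 43%, 57% and 78%. Rank sum power stayed at about 35%, 34% and 31–32% throughout.

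**The case against.** The strongest reply is that this is a slip of naming. The previous sentence has already assigned Mann–Whitney to independent groups. An author who then places a Wilcoxon test beside the paired t test very probably means signed-rank, and the section is loosely worded throughout. This stands in part: P values go wrong only if the printed name is followed, and the article cannot settle what was meant. It does not remove the need for a correction, because an analyst or reader has only the printed name and the two tests are different procedures.

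The unclear opening of the sentence could also be read as referring to the control arm alone. The paired t test beside it shows that before-after data are meant on either reading.

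A second reply is that the reach is narrow. This stands in full. Objective 1 (2.2) compares SDBG and CV between the two groups, and those comparisons use the independent t test or Mann–Whitney, which suit independent arms.

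A reader might infer more than the article supports:

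- **That the primary result is compromised, or that a false efficacy claim could follow.** It could not follow from this error: the between-group tests are unaffected, and under positive correlation the error makes significance harder to reach.
- **That the plan judges efficacy on within-group P values.** The section only lists a within-group test. The Efficacy evaluation section does not say that efficacy rests on it, and the stated objective is between-group.

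**Conclusion.** As printed, the test named for non-normal within-group comparisons does not fit paired data. Whether any P value will actually be wrong depends on whether the name or the evident intention is followed.

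If the name is followed, the cost at 24 pairs is a type I error of about 2%, 1% and 0.1% in place of 5%. Power is about 35%, 34% and 32%, against roughly 43–48%, 57–61% and 76–82% with the signed-rank test. These figures rest on assumed correlations of 0.3, 0.5 and 0.7, an assumed 0.5 SD log-scale shift and log-normal data. The direction needs only a positive correlation between a participant's repeated values.

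This is a definite but limited error that should be corrected. It is conservative and confined to non-normal within-group comparisons.

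**What to change.** Replace the sentence in Statistical analysis (4.5) with: *Within each group, normally distributed variables are compared by paired t test and non-normally distributed variables by Wilcoxon signed-rank test.*

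This corrects the test name and clears up which comparison is meant. It costs one sentence and changes neither the sample size, the data collected nor the between-group analysis. If signed-rank was intended all along, the change only makes the text say so.
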